### Outcomes measurement

The primary outcome of the study is the changes of the echocardiographic indices of LV remodeling, which is the LV volume index at end-systolic and end-diastolic time as measured by modified Simpson's rule [25], during the study period. Echocardiographic records from participating institute are sent to the core echocardiography laboratory for the analysis. Secondary outcomes include occurrence of predefined clinical events (all-cause death, cardiovascular death, hospitalization, revascularization), changes of plasma level of neurohormone (B-type natriuretic peptide, norepinephrine, aldosterone), and echocardiographic indices other than ventricular volume (ejection fraction, wall motion score index, mitral inflow, tissue Doppler index) at 12 months (Table 2). Neurohormone measurement will be conducted in a core laboratory.

**Table 2 T2:** Study Objectives

Primary Objective	Secondary objectives
Change in the LV index measured by echocardiography from baseline to follow-up	Change in functional capacity (NYHA class)

	All cause mortality

	Cardiovascular death

	Hospitalization

	Revascularization procedures (emergency and elective)

	Change in B-type natriuretic peptide (BNP) level

	Change in plasma norepinephrine level

	Change in serum aldosterone level

	Change in ejection fraction

	Change in MI index (wall motion score index)

	Change in sphericity index

	Change in mitral inflow index (mitral E/A ratio, mitral deceleration time)

	Change in tissue Doppler index (mitral Ea)

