### Sample size

The sample size calculation is based on the primary outcome and the primary analysis for the intention-to-treat population. In the VALIANT Echo study, [17] a sample size of 600 patients was determined necessary to detect, with a 90% power, a 7.6 mL difference in end-diastolic volume between the treatment groups. Because the present study enrolls more patients with mild degree (EF < 50%) LV dysfunction, we anticipate that the difference of ventricular volume between treatment groups will be smaller than the previous study. Thus, detection of 3.8 mL difference, with a two-sided level of significance α = 5% and a power of 1-β = 90%, in end-diastolic volume between treatment groups would require a sample size of 279 patients in a usual dose of valsartan group and 558 patients in a high dose valsartan group. Assuming 25% of patients are lost to follow-up or with missing data, as reported in the GISSI-3 study [27], the required sample size of this study will be a total of 1,116 patients. The study is likely to be underpowered in terms of assessing secondary outcomes if this size is employed. Variability data for the outcome measures could be used to inform design a subsequent larger-scale randomized controlled trial, if post hoc analysis reveals this study to be underpowered.

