### Statistical analyses

A consultant group of statisticians has been appointed to conduct the statistical work for this study, including data completion, interim analysis, application of statistical technique and final assessment. The principal analysis will be an intention-to-treatment basis. For baseline characteristics, continuous variables are assessed using the Student *t *test and discrete variables are compared using the chi-square test. The two-sided null-hypothesis for the primary outcome measure states that usual and high dose valsartan lead to the same expected change of ventricular remodeling during the 12 months after MI. This null-hypothesis will be tested by application of an analysis of covariance that adjusts for age, gender, and cardiovascular risk factors. Primary outcome will be compared using 2-sample *t *tests. Event-free cumulative survival rates are plotted using the Kaplan-Meier method and comparisons are made between patients with and those without clinical events using the log-rank test. A Cox proportional hazards model with the use of forward selection based on the likelihood ratio test will be implemented for multivariate analysis to determine which prognostic factors identified in the univariate analysis were significantly related to 12-month clinical events. Assessments for the change of neurohormone and other echocardiographic indices will be compared between treatment groups at 12-month follow-up using 2-sample *t *tests.

We will compare proportions of missing data using chi-square tests and agreement between data collection methods using Lin's Concordance Correlation Coefficient. Additionally, sensitivity analyses will be conducted using different patient populations (per protocol population excluding patients with relevant protocol violations), different imputation techniques for missing values, and different statistical methods for taking into account covariates. A value of p < 0.05 will be considered statistically significant.

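### Prognostic factors for clinical events would be declared significant after univariate screening and forward selection, at an unadjusted p < 0.05 that ignores the selection

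*Protocol article*

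**What the plan says.** The Statistical analyses section of the protocol article fixes a two-stage procedure for the clinical events. Factors are first picked out one at a time. They then go into a stepwise model: "A Cox proportional hazards model with the use of forward selection based on the likelihood ratio test will be implemented for multivariate analysis". The stated purpose is "to determine which prognostic factors identified in the univariate analysis were significantly related to 12-month clinical events". One threshold closes the section and covers everything in it: "A value of p < 0.05 will be considered statistically significant".

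The section does not list or count the candidates, and it gives no separate threshold for the univariate screen or for entry into the model. It attaches no adjustment, shrinkage, validation or exploratory label to this analysis.

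The events are a secondary outcome (Outcomes measurement, Table 2). The Sample size section warns: "The study is likely to be underpowered in terms of assessing secondary outcomes if this size is employed". The primary outcome is handled separately, by analysis of covariance and t tests.

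**The concern.** A likelihood-ratio p-value refers the statistic to a chi-square distribution with 1 degree of freedom. That is the right reference for one factor named in advance. Forward selection instead tests the largest statistic among all remaining candidates, and the final model prints p-values as if each surviving factor had been the only one considered. The screen and the selection also use the same events that the final model then reports on.

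Three results follow. The chance of calling some unrelated factor significant exceeds 5%. Confidence intervals are too narrow because they ignore the uncertainty about which factors enter. Hazard ratios of the factors that enter are biased away from 1, because a factor enters only when its estimate happens to be large enough. The low power that the article concedes for secondary outcomes makes this last effect worse.

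At stake is the reliability of any statement that a given factor is significantly related to 12-month events.

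**Working it through.** **Figure in the plan.** There is none to reproduce. The article states no error rate, candidate count or expected number of events for the Cox analysis.

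**Inputs**
- Procedure and general p < 0.05: Statistical analyses section.
- Sample size 1,116: Sample size section.
- Number of candidates k: not stated; assumed 5 to 20.
- Entry threshold: not stated; assumed p < 0.05.
- Correlation between candidates: not stated; assumed 0 to 0.5.
- 12-month event rate: not stated; assumed 5% to 20%, for the checks only.

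**Formula.** Suppose no candidate is related to events. Forward selection then enters at least one factor exactly when the smallest univariate likelihood-ratio p-value is below 0.05. A prior screen at the same or a looser threshold does not change this probability. For k independent candidates it is 1 − 0.95^k:
- k = 5: 1 − 0.95^5 = 22.6%
- k = 10: 1 − 0.95^10 = 40.1%
- k = 14: 1 − 0.95^14 = 51.2%
- k = 20: 1 − 0.95^20 = 64.2%

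It reaches 50% at k = ln(0.5)/ln(0.95) = 13.5.

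**Correlated candidates.** Probability that the largest of k equally correlated normal statistics exceeds 1.96 in absolute value (200,000 draws; the row for correlation 0 is the formula):

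| Correlation | k = 5 | k = 10 | k = 14 | k = 20 |
|---|---|---|---|---|
| 0 | 22.6% | 40.1% | 51.2% | 64.2% |
| 0.3 | 20.9% | 35.0% | 43.9% | 53.9% |
| 0.5 | 18.2% | 28.8% | 34.9% | 41.8% |

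The range is therefore about 18% to 64%. Even the lowest value is 18.2/5 = 3.6 times the single-test rate.

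**Check with actual Cox fits.** Null trials were simulated with n = 1,116, independent candidates (half binary, half continuous), likelihood-ratio tests and event rates of 5%, 10% and 20%, with 600 runs each. At least one false factor appeared in 21–23% of runs for k = 5, 40–41% for k = 10, 50–52% for k = 14 and 65–66% for k = 20. The error of a single test was 5.0%, so the inflation comes from taking the best of several tests and not from the Cox approximation. The event rate made no material difference.

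**Some factors truly prognostic.** If, for illustration, 5 of 15 candidates are real, 10 null ones remain. The chance of at least one spurious entry is then roughly 1 − 0.95^10 = 40%. This treats the null candidates as independent. It was not simulated, and a strict univariate screen would lower it somewhat.

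**Hazard ratios.** An unrelated continuous factor that enters first must have an estimated log hazard ratio of at least about 1.96 standard errors. Per standard deviation of the factor, the standard error is about 1/√(events).
- 5% event rate: 1,116 × 0.05 = 55.8 events; 1.96/√55.8 = 0.262; hazard ratio at least exp(0.262) = 1.30, or its inverse.
- 20% event rate: 1,116 × 0.20 = 223.2 events; 1.96/√223.2 = 0.131; hazard ratio at least exp(0.131) = 1.14, or its inverse.

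The true value in both cases is 1. These figures assume full follow-up and are only an order of magnitude.

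**The case against.** The strongest reply is that this is a general objection to stepwise selection, aimed at a minor analysis. Finding predictors is not among the objectives in Table 2. The article promises no familywise error rate for prognostic factors, and it already warns about power for secondary outcomes. A candidate list, sizing to events and validation normally sit in an analysis plan that is not shown. Much of this stands. The absence of those details is not a fault, and the stakes are low. But the selection method and the purpose of declaring significance are fixed in the article, so an analysis plan that follows it inherits the problem. The power warning does not address selection.

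Three stronger readings are tempting and are not supported.

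- **That about half of such analyses would report a false factor.** This needs 13 to 14 independent candidates, or about 15 to 20 at correlations of 0.2 to 0.3. One could reach 15 by counting the echocardiographic, neurohormonal and functional measures in the outcomes section and Table 2 and adding age, gender and dose. But those measures appear there as outcomes, mostly changes from baseline, and nothing names them as Cox candidates. Several are also linked: ejection fraction is calculated from the two ventricular volumes.
- **That no factor is related to events.** The Background links remodeling to poor prognosis and, in heart failure, neurohormone level to mortality. The global null is therefore a reference case and not a forecast. Inflation does not depend on it, as the mixed case shows.
- **That the trial's main conclusion, or planned claims about particular neurohormonal or echocardiographic predictors, is at risk.** The primary test does not use this model, and no such predictor claims are announced.

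**Conclusion.** The point holds as a flaw in a method that the article itself fixes. Following the text as written gives post-selection p-values, intervals and hazard ratios that should not be read at face value. The chance of at least one spurious factor is well above 5% for any plausible number of candidates. No single figure can be attached to it, because the count, their correlation and the entry threshold are all assumed here. The direction of the hazard-ratio bias is certain, but its size depends on the number of events. The consequence is confined to a secondary prognostic analysis and does not touch the type I error of the primary endpoint. This is a worthwhile improvement, not a threat to the trial.

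**What to change.** Replace the sentence on forward selection with wording such as: Clinical events within 12 months will be analysed with one Cox model containing randomized dose and a short set of prognostic factors fixed before outcome data are seen, their number chosen in view of the expected events; all hazard ratios will be reported with 95% confidence intervals, whether or not significant.

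If selection is kept, repeat the entire screening and selection procedure in bootstrap samples and report optimism-corrected or penalised estimates. Label the result exploratory and make no p < 0.05 claims from it.

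The cost is a change of wording and slightly more analysis work. The clinical team must agree the factor list in advance, and fewer factors will be called significant.

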## Methods and Design

### Study design

VALID is a prospective, multicenter, randomized, open-label, active controlled study with two parallel study groups. VALID is being conducted in 18 tertiary hospitals throughout South Korea. Participants are randomly allocated into the usual dose group and high dose group and followed-up for 12 months after discharge. Overall study algorithm is depicted in Figure 1. Baseline echocardiographic examination and neurohormonal assay are performed before discharge. Study approval was given by the institutional review board at each participating center, and consecutive, eligible patients are provided written informed consent.

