### Randomization

Randomization will take place following initial echocardiographic estimation of left ventricular ejection fraction, which is conducted after stabilization by reperfusion therapy or conservative treatment. Eligible patients are randomly assigned in a 1:2 ratio to receive the usual dose (valsartan 80 mg/day) or a high dose (valsartan up to 320 mg/day). Random allocation with stratified technique is generated automatically by a centralized web based tool (http://www.cnrres.co.kr/valid) so it cannot be influenced by researchers.

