### Intervention and comparator descriptions

Eligible patients are randomly assigned in a 1:2 fashion to either the usual dose group (valsartan 80 mg/day) or the high dose group (valsartan up to 320 mg/day). In the usual dose group, valsartan 40 mg twice a day is administrated throughout the study period. For those in the high dose group, dose is up-titrated to 80 mg twice a day before hospital discharge and finally to 160 mg twice a day after 2 weeks during outpatient visits. The process of the trial conduct is illustrated in Figure 2. If up-titration is not clinically feasible, either because of hypotension or deepening azotemia, the previous dose is administered subsequently as maximal tolerable dose.

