### Follow-up protocol

During the study period, study visits are scheduled at week -2 (high-dose group only), and 1, 3, 6, 9, 12 months. At each visit, patients undergo a complete physical examination, medical history-taking, and assessment of drug compliance. Investigators evaluate all clinical and laboratory adverse events at each visit. To monitor safety, serum creatinine and urea nitrogen concentrations are determined at every study visit. New York Heart Association (NYHA) functional class [26] and predefined clinical events are recorded at each clinical visit. Echocardiographic examination and neurohormonal assay are performed at 3 and 12 months after discharge. After a routine review with 50% of the patients enrolled, early cessation of the trial will be decided by the institutional review board and study sponsor when the trial appears to be futility or causing unexpected harm to participants.

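### Neurohormone change is tested by an unadjusted t test, and the baseline sample is not required to precede randomised dosing

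*Protocol article*

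**What the plan says.** All references are to the protocol article.

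- **Outcome.** Outcomes measurement lists among the secondary outcomes "changes of plasma level of neurohormone (B-type natriuretic peptide, norepinephrine, aldosterone").
- **Test.** Statistical analyses: "Assessments for the change of neurohormone and other echocardiographic indices will be compared between treatment groups at 12-month follow-up using 2-sample" t tests. No covariate and no measurement scale are named. The only analysis of covariance in that section is for the primary null hypothesis. It adjusts for age, gender and cardiovascular risk factors.
- **Baseline timing.** Study design: "Baseline echocardiographic examination and neurohormonal assay are performed before discharge".
- **Randomisation timing.** Randomization: "Randomization will take place following initial echocardiographic estimation of left ventricular ejection fraction". Nothing ties the blood sample to randomisation or to the first dose.
- **Dosing before discharge.** Intervention and comparator descriptions: "For those in the high dose group, dose is up-titrated to 80 mg twice a day before hospital discharge"; and for the other arm, "In the usual dose group, valsartan 40 mg twice a day is administrated throughout the study period".
- **Follow-up assays.** Follow-up protocol: "Echocardiographic examination and neurohormonal assay are performed at 3 and 12 months after discharge".
- **Power.** Sample size concedes that the study is probably underpowered for secondary outcomes.

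**The concern.** The abstract gives neurohormone change as an aim of the study, and the assays are run in a core laboratory. Two features of the plan weaken that comparison.

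First, a two-sample t test on change gives the baseline value a fixed coefficient of one instead of estimating it. When the correlation between baseline and 12 months is below one, this adds noise that an ANCOVA would remove at no cost in patients or samples. A trial that already expects low power for these outcomes has good reason not to give that precision away.

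Second, a change score is only as clean as its baseline. If the baseline sample is taken after the arms have started to receive different doses, part of the treatment effect may sit in the baseline and is subtracted from the result. An analysis cannot fully restore it afterwards.

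**Working it through.** **Inputs from the article.** Evaluable patients: 279 usual dose and 558 high dose. The article's inflation reproduces: (279 + 558)/0.75 = 837/0.75 = 1,116. That size was set on end-diastolic volume; the article gives no effect, SD or correlation for any neurohormone.

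**Assumed inputs.** Correlation r between baseline and 12 months of 0.3 to 0.7; equal SD at the two times; for the power illustrations, log-normal values, log-SD 0.5 or 1.0, and a 12-month high/usual ratio of 0.80.

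**Step 1: precision on a common scale.**
- Variance of change: 2σ²(1 − r).
- Residual variance of ANCOVA on baseline: σ²(1 − r²).
- Ratio, ANCOVA to change: (1 − r²)/[2(1 − r)] = (1 + r)/2.

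| r | ANCOVA/change variance | Saving | ANCOVA power where the change t test has 80% |
|---|---|---|---|
| 0.3 | 0.65 | 35% | 93.5% |
| 0.5 | 0.75 | 25% | 89.9% |
| 0.7 | 0.85 | 15% | 86.0% |

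The last column is Φ[(1.960 + 0.842)/√((1 + r)/2) − 1.960].

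**Step 2: scale, conditional on untransformed analysis.** Simulated power at 279:558, ratio 0.80, r = 0.5, baseline taken before dosing:

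| Log-SD | Overall trend from baseline | Raw change t | Log change t | Log ANCOVA |
|---|---|---|---|---|
| 1.0 | none | about 53% | about 86% | about 94% |
| 1.0 | levels halve | about 20% | about 86% | about 94% |
| 0.5 | none | over 99% | over 99% | over 99% |
| 0.5 | levels halve | about 82% | about 100% | about 100% |

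The penalty for raw values therefore depends heavily on skewness and on the overall trend, and the article gives neither. Under the null (log-SD 1.0, r = 0.5, levels halving) the raw change t test rejected in 4.7% of 3,000 runs, so it remains valid.

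**Step 3: what the timing rules allow.** Set side by side:
- the baseline assay is at any time before discharge;
- randomisation follows the initial echocardiogram, with no link to the blood sample;
- the high-dose arm reaches 80 mg twice a day before discharge, while the usual-dose arm stays on 40 mg twice a day.

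A sample drawn on the day of discharge meets every rule and can fall when the arms are on 160 and 80 mg/day. A sample drawn before the first randomised dose also meets every rule. The text permits both.

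**Step 4: consequence if the sample is late.** Let f be the share of the 12-month log-scale effect already present at baseline (assumed; the article has no data on it). The change score estimates (1 − f) of the effect. ANCOVA on the same baseline estimates (1 − r·f). Take r = 0.5, log-SD 1.0 and ratio 0.80, so the effect is |ln 0.80| = 0.223. The standard error is √(1/279 + 1/558) = 0.0733 for log change, since 2(1 − r) = 1, and 0.0733 × √0.75 = 0.0635 for ANCOVA. Power is Φ(estimated effect/SE − 1.960).

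| f | Change estimates | Power, log change | ANCOVA estimates | Power, log ANCOVA |
|---|---|---|---|---|
| 0 | 100% | 86% | 100% | 94% |
| 0.25 | 75% | 63% | 87.5% | 87% |
| 0.5 | 50% | 33% | 75% | 75% |

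Baseline adjustment softens the attenuation but does not remove it. Only a sample taken before randomised dosing does.

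**The case against.** **The scale.** A reader might infer that the t tests are on raw concentrations, since the outcome is described as a change in plasma level and no transformation is named. The article does not say so. A t test on change in log values fits the same sentence, and the choice of scale is commonly left to an analysis plan. Silence on scale is therefore not itself a fault, and Step 2 stands only as a conditional illustration.

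**The doses at baseline.** A reader might also infer that the arms are already on different doses when the baseline is taken, and so that the contrast is biased toward no difference. The documents do not support that either. A late sample is permitted, not prescribed. The word up-titrated suggests a lower starting dose in the high-dose arm, so even a sample after randomisation may precede divergence. Attenuation further needs an early effect of the same sign as the 12-month effect. With a pre-dose sample the change score is unbiased and loses only precision. The in-hospital contrast (160 against 80 mg/day) is also smaller than the later one (up to 320 against 80 mg/day).

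**The impact.** The endpoints are secondary, low power is conceded, and the test is valid. The article also promises sensitivity analyses with other ways of handling covariates. These points limit the severity. The promise, however, is generic: it names neither these endpoints nor the baseline value, and it leaves the unadjusted t test as the stated comparison.

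**What remains.** The unadjusted test is a stated choice, not an omission, and the baseline window as written does not require a pre-dose sample.

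**Conclusion.** The point holds in a limited form. The named analysis of neurohormone change is less precise than an ANCOVA on data already in hand: the ANCOVA variance is lower by 15% to 25% at assumed correlations of 0.7 to 0.5, whatever the common scale. A larger loss follows only if values are analysed untransformed and are strongly skewed.

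The baseline window allows a sample after the doses diverge. If that happens and the early effect has the same sign, the change score estimates only (1 − f) of the 12-month effect, for example 75% of it at an assumed f of 0.25. Neither the timing nor f can be established from the article, so attenuation is a risk and not a demonstrated bias. Type I error is not at issue. The change is worth making because it is cheap, but it concerns secondary endpoints and does not threaten the trial's main conclusion.

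**What to change.** 1. Replace the two-sample t test for BNP, norepinephrine and aldosterone with an ANCOVA of the log-transformed 12-month value on treatment and log-transformed baseline value. Report geometric mean ratios with 95% confidence intervals.
2. Define the baseline sample as the last one taken before the first dose of randomised study drug, and record the sample time relative to that dose.
3. Flag baselines taken after that dose and exclude them in a sensitivity analysis.

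Cost: a change of analysis wording and a timing instruction for a sample the trial already takes. No patients, visits or assays are added. The downside is that results are read as ratios and not as absolute changes in concentration.
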